## Abstract

**Background:**

With a worldwide increase in the elderly population, and an associated increase in health care utilization and costs, preventing avoidable emergency department visits and hospitalizations is becoming a global priority. A personal emergency response system (PERS), consisting of an alarm button and a means to establish a live connection to a response center, can help the elderly live at home longer independently. Individual risk assessment through predictive modeling can help indicate what PERS subscribers are at elevated risk of hospital transport so that early intervention becomes possible.

**Objective:**

The aim is to evaluate whether the combination of risk scores determined through predictive modeling and targeted interventions offered by a case manager can result in a reduction of hospital admissions and health care costs for a population of German PERS subscribers. The primary outcome of the study is the difference between the number of hospitalizations in the intervention and matched control groups.

**Methods:**

As part of the Sicher Zuhause program, an intervention group of 500 PERS subscribers will be tracked for 8 months. During this period, risk scores will be determined daily by a predictive model of hospital transport, and at-risk participants may receive phone calls from a case manager who assesses the health status of the participant and recommends interventions. The health care utilization of the intervention group will be compared to a group of matched controls, retrospectively drawn from a population of PERS subscribers who receive no interventions.

**Results:**

Differences in health care utilization and costs between the intervention group and the matched controls will be determined based on reimbursement records. In addition, qualitative data will be collected on the participants’ satisfaction with the Sicher Zuhause program and utilization of the interventions offered as part of the program.

**Conclusions:**

The study evaluation will offer insight into whether a combination of predictive analytics and case manager-driven interventions can help in avoiding hospital admissions and health care costs for PERS subscribers in Germany living at home independently. In the future, this may lead to improved quality of life and reduced medical costs for the population of the study.

**Trial Registration:**

Deutsches Register Klinischer Studien (DRKS), DRKS00017328; https://www.drks.de/drks_web/navigate.do?navigationId=trial.HTML&TRIAL_ID=DRKS00017328

**International Registered Report Identifier (IRRID):**

DERR1-10.2196/17584

## Introduction

With the worldwide increase in the elderly population [1], chronic diseases and associated health care utilization, such as costly emergency department visits and subsequent hospitalizations, are also on the rise. Elderly patients >75 years of age account for up to a third of ambulance transports in Germany [2]. Following worldwide trends, German elderly aged 65-74 years, on average, show a 50% increase in health care expenditures compared to the 50-64 age bracket. For the elderly aged 75 and over, the increase is 100% [3]. Preventing avoidable emergency department visits and admissions in elderly patients is becoming a global priority [4,5] since emergency hospitalizations are particularly distressing for the elderly and have been associated with adverse events such as hospital-acquired infections, loss of functional independence, and falls [6].

A Personal Emergency Response System (PERS) service consists of a help call button worn by the subscriber on the wrist or as a pendant. When a PERS subscriber requires assistance, a press of the button will establish a live connection to a personal response agent in a response center. The agent is then able to triage the event, and when applicable, assist the subscriber, either over the live voice connection, or by contacting a relative, informal caregiver, care provider, or emergency services.

The main benefit of a PERS service is the reassurance that help will always be available in case of an emergency, such as a fall or respiratory issues. Previous studies in the United States (US) [7,8] have shown that PERS data can be used to develop prediction models of decline in patient status. Such models thus provide early warning signs of impending emergencies and can be used by case managers to provide timely intervention [9]. Currently, it is unknown whether the combination of predictive modeling and case manager interventions is also effective in Germany, with a different health care system and potentially a different PERS subscriber population compared to the US. Whereas the US health care system is characterized by vertically integrated care providers and a strong private pay mentality, the German system is fragmented with very limited ability of health insurances to create and enforce care pathways.

Risk prediction can play an important role in preventing future hospitalization by allowing an opportunity for timely interventions and can play an instrumental role in reducing health care costs and utilization [10-13]. In the Sicher Zuhause (Safe at Home) study, the risk scores are used by a case manager (along with other data such as demographics, medical alert history, or medical conditions) to determine participants potentially at risk of hospitalization in a German PERS subscriber population. The case manager may then proactively contact the at-risk participant, and if needed, intervene at an early stage, before hospitalization becomes inevitable.

### Objectives

The aim of the Sicher Zuhause study—a collaborative effort by Philips, the Techniker Krankenkasse (TK), ServiceCall AG, and the German Red Cross (DRK)—is to evaluate whether the combination of risk scores determined through predictive modeling and targeted interventions offered by a case manager can result in a reduction of hospital admissions and health care costs in a German PERS subscriber population. The primary study aim is to determine whether there is a difference in the number of hospitalizations between the intervention group and the control group over the 8-month intervention period.

In addition, the study aims to assess several secondary outcomes; these are the impact on the number of hospitalizations leading to admissions, the number of days admitted to a hospital, the number of ambulatory visits, the hospital-related costs, and the overall health care costs. Further, qualitative data collected through questionnaires will be used to assess the participants’ satisfaction with the PERS devices used in the study and with the Sicher Zuhause program as a whole.

## Methods

### Study Design and Overview

The Sicher Zuhause study is a prospective interventional study with an intervention arm of 500 participants, which is compared to a matched population derived from historical PERS subscribers. The study tracks the health care utilization and expenditure of the participants over 8 months. During this period, the participants in the intervention arm may receive calls from one of the case managers in the study with the offer to discuss the participant’s health status and care needs. Based on this discussion, the case manager may recommend one or more interventions.

The matched population serving as a control group does not actively take part in the study and is instead derived from the historical records of PERS subscribers. This population will be matched with the intervention arm to be as similar as possible compared to the intervention group using propensity score matching. An overview of the study design is shown in Figure 1.

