### Enrollment

Potential study participants will be recruited through one of several ways:

New PERS customers or customers of the nursing service of ServiceCall or the DRK who are insured at the TK will be asked if they are interested in learning about the study.Potential participants may be made aware of the study through articles published by the TK (for example, in their member magazine).Potential participants may be identified from among existing TK customers. These potential participants may be contacted directly by the TK by phone or mail.

Identified individuals will be sent an information letter and informed consent. Individuals will be enrolled in the study after returning the signed informed consent letter.

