#### Data Analysis

The analysis of the primary outcome, the number of hospitalizations, will be based on a comparison of reimbursement records between the intervention arm and a matched population acting as a control group. Propensity score matching will be used to obtain a comparable control group [14,15] using a large pool of population characteristics (over 100 variables), which include the age at enrollment, gender, geographic location, care level, and presence or absence of common medical conditions. The intervention arm of 500 participants will be compared to an equal-sized matched control group of 500, determined by propensity score matching out of an initial pool of approximately 5000 candidates. Differences between groups will be analyzed through statistical testing, using the binomial rate test for the number of admissions and the t-test for differences in costs.

Analysis of the qualitative data provided by questionnaires will focus on evaluating the participants’ satisfaction with the Sicher Zuhause program overall, and with the individual components such as the case manager interactions and the offered interventions. This will be done through descriptive statistics such as the mean and standard deviations of the satisfaction and helpfulness measured on Likert scales.

The qualitative data will be used to provide insights into to outcomes of the primary objectives and may assist in the improvement of the CareSage predictive model.

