## Results

The enrollment of participants began mid-2019 and is expected to be complete by end of 2020. Enrollment is expected to take longer than usual based on the number of new PERS subscribers over time in the geographical area covered by the response centers in the study. Data collection is expected to be completed by summer of 2020. Initial results are expected to be available in fall of 2021.

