## Discussion

This protocol describes a study that aims to determine if the combination of risk scores determined through predictive modeling and interventions offered by a case manager can result in a reduction of hospital admissions and health care costs in a German PERS subscriber population. The rapidly aging population with multiple comorbidities presents numerous challenges to effective care management, and therefore, alternatives to hospital and institutional care are needed to optimize health care costs and improve patient outcomes [17]. In the future, the results of this study can lead to better health outcomes for the population described.

This study has a few limitations. First, it does not include a randomized design, and the use of a retrospective control group may lead to selection bias. In the study, this concern is partially addressed by the use of propensity score matching. Second, the effect of the risk prediction and the interventions cannot be easily separated. As such, the study aims to evaluate the combination of the two, where the predictive model helps to identify the right subset of participants to whom interventions should be offered. Further, analysis of the qualitative data can help to provide insights into the performance of the predictive model and the effectiveness of the interventions. Another option would be to include additional study arms; however, due to the expected recruitment rate, this is likely not feasible.

A third limitation is that it might be difficult to capture data on health care utilization that may be initiated outside of the PERS service. Capturing emergency department visits and hospitalizations is important because the study population is a high health care utilization group that is at risk for emergency transport, and patients are typically taken to the nearest medical center for emergency care services. However, self-reported data from patients may help mitigate some of these challenges.

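### Controls are drawn from historical PERS subscribers with no stated observation window, so calendar period may be confounded with the programme and nothing named in the plan adjusts for it

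*Protocol article*

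**What the plan says.** Study Design and Overview in the protocol article calls the controls historical twice: the intervention arm is one "which is compared to a matched population derived from historical PERS subscribers", and the control group is "derived from the historical records of PERS subscribers". The Methods paragraph of the Abstract says the controls are "retrospectively drawn from a population of PERS subscribers who receive no interventions". The Objectives state the primary comparison as a "difference in the number of hospitalizations between the intervention group and the control group over the 8-month intervention period".

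The intervention arm is prospective. Under Results, "The enrollment of participants began mid-2019 and is expected to be complete by end of 2020", and each participant is then followed for 8 months.

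Data Analysis describes 1:1 propensity score matching of 500 participants to 500 controls, from a pool of about 5000 and on more than 100 variables. Those named are "age at enrollment, gender, geographic location, care level, and presence or absence of common medical conditions". The planned tests are a binomial rate test for admissions and a t-test for costs.

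The Discussion accepts that a retrospective control group may bring selection bias and adds: "In the study, this concern is partially addressed by the use of propensity score matching". It does not mention calendar period, season or trend over time.

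**The concern.** Propensity matching balances measured characteristics where both groups have people with similar values. If every participant is observed in one calendar period and every control in an earlier one, period determines the arm. There is then no overlap on time to match within, and neither more patient variables nor a larger pool would create it. The two planned tests have no period term.

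Any change between the periods in admission practice, access to care, coding or prices would then appear as a programme effect. Season matters too: follow-up lasts 8 months rather than 12, so seasonal variation does not average out within a person unless start months are aligned. The primary outcome and all utilization and cost comparisons are exposed.

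**Working it through.** **1. Calendar windows.**

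| | Intervention arm | Control arm |
|---|---|---|
| Entry | mid-2019 to end of 2020 | not stated |
| Follow-up | 8 months each | calendar dates not stated |
| Last follow-up | end of 2020 + 8 months = about August 2021 | not stated |

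The August 2021 date is simple addition. Results also expects data collection to finish by summer 2020, before enrolment ends, so the participants' own window is not firm.

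**2. The plan's own figure.** Sample Size Calculation uses 32% against 23% over 180 days, 80% power and alpha 0.05. With the two-sided pooled formula,

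n = [1.960 × √(2 × 0.275 × 0.725) + 0.842 × √(0.32 × 0.68 + 0.23 × 0.77)]² / 0.09² = 385.2, rounded up to **386**.

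This matches the article, so the sample-size arithmetic is not at issue. Power is 89.1% at 500 per arm. After the planned 15% loss, 500 × 0.85 = 425 per arm, and power is 83.7%.

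**3. Downward drift with no programme effect (drift assumed).** Let the control rate be pC = 0.32 and the participants' rate pT = 0.32 × (1 − drift), with mean p̄. The chance of a significant result favouring the programme is

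Φ[(−1.960 × SE₀ + pC − pT) / SE₁], with SE₀ = √(2p̄(1 − p̄)/n) and SE₁ = √((pC(1 − pC) + pT(1 − pT))/n).

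For 10% drift and n = 500: pT = 0.288, p̄ = 0.304, SE₀ = 0.02909 and SE₁ = 0.02907. This gives Φ[(−0.05702 + 0.03200)/0.02907] = Φ(−0.861) = 0.195.

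| Assumed relative fall | pT | 425 per arm | 500 per arm |
|---|---|---|---|
| 0% | 32.0% | 2.5% | 2.5% |
| 5% | 30.4% | 7.3% | 7.9% |
| 10% | 28.8% | 17.2% | 19.5% |
| 15% | 27.2% | 33.4% | 38.3% |
| 20% | 25.6% | 54.0% | 60.8% |

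**4. Upward drift with the planned effect present (drift assumed).** A 10% relative rise moves the participants' rate from 23% to 0.23 × 1.10 = 25.3%, while the historical controls stay at 32%. At n = 500, SE₀ = 0.02860 and SE₁ = 0.02852. Power is Φ[(−0.05605 + 0.06700)/0.02852] = Φ(0.384) = 0.650, down from 0.891.

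**5. Limits of the illustration.** The rates are 180-day proportions standing in for 8 months. The primary outcome is a number of hospitalizations under a binomial rate test, whereas these figures use a two-proportion test. They show the order of size only.

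**The case against.** The strongest reply is that non-overlap is inferred. Historical records may simply be existing records extracted later. The Abstract's description of subscribers who receive no interventions is in the present tense, and the Objectives refer to the 8-month intervention period for both groups. Figure 1, which shows the study design, is not available here and may give the timeline. This stands: a reader might infer that the controls certainly come from an earlier period and that matching can never remove the confounding, but the documents do not establish this. If the windows overlap, matching on start month would be possible. Historical is still the article's word for the controls, and nothing in it places them in the participants' period.

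A reader might also infer that time since PERS start differs between the groups, because new PERS customers are one recruitment route. The article does not say how control index dates relate to PERS start, and new customers are only one of several routes listed under Enrollment. The list of more than 100 variables is open, so PERS tenure, season or prior utilization may be on it. That imbalance is not shown and is not claimed here.

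The retrospective control is a declared trade-off, with matching described as only a partial answer. This too stands, but the bias named is selection bias, and the remedy offered does not act on calendar period.

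Finally, both the size and the direction of drift are unknown. That is why both directions appear above.

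**Conclusion.** The point holds conditionally. As written, the article calls its controls historical, gives them no calendar window, and names no matching variable or test term that deals with period. To the extent that the control period is earlier and does not overlap, period is confounded with arm and matching on patient characteristics cannot separate the two.

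Under an assumed 10% relative fall, the falsely favourable tail rises from 2.5% to about 17-20%. Under an assumed 10% rise, power at 500 per arm falls from about 89% to 65%. The documents supply no drift figure, so these results do not show that the trial is biased or that any bias favours the programme. The case for acting is that the exposure reaches every between-group comparison and that most of it can be removed at extraction.

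**What to change.** - In Data Analysis, state the controls' observation window. Assign each control an index date in the same calendar month, or at most the same quarter, as its matched participant. Take controls from insured PERS subscribers not in the programme during that period.
- Where only earlier windows are available, extract pre-index hospitalizations and costs for both groups and use a difference-in-differences with a period-trend adjustment. The pre/post contrast removes stable differences in level. The trend adjustment is needed because the two groups' windows still differ.
- In the Discussion, name period and seasonal effects as a limitation separate from selection bias.
- In Results, reconcile the completion of data collection (summer 2020) with the end of enrolment (end of 2020), so that the windows can be aligned.

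Cost: controls are not enrolled, so this changes the extraction from existing insurer records and adds some analysis. The planned sample size is unaffected. The pool may fall below 5000 for the 500 matches. Concurrent subscribers who did not join may differ from volunteers; pre-index utilization should help to control that.

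### If the historical controls are observed before the programme, calendar period coincides with group and matching on personal characteristics cannot remove it; the control window should be dated and aligned

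*Protocol article*

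**What the plan says.** Study Design and Overview sets up a prospective intervention arm "which is compared to a matched population derived from historical PERS subscribers" and adds that the control group is "derived from the historical records of PERS subscribers". The Methods paragraph of the Abstract describes the controls as "retrospectively drawn from a population of PERS subscribers who receive no interventions". No section gives dates for the control observation period.

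For the intervention arm, the Results section states: "The enrollment of participants began mid-2019 and is expected to be complete by end of 2020". The same paragraph states: "Data collection is expected to be completed by summer of 2020". Follow-up is fixed per person: "The study tracks the health care utilization and expenditure of the participants over 8 months".

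Data Analysis matches 500 controls from a pool of about 5000 on more than 100 characteristics, "which include the age at enrollment, gender, geographic location, care level, and presence or absence of common medical conditions". It then applies a binomial rate test to admissions and a t-test to costs. No term for period is described. The Discussion names selection bias as the consequence of the retrospective control and says: "In the study, this concern is partially addressed by the use of propensity score matching". It does not mention calendar time.

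**The concern.** A propensity score balances variables on which the two groups overlap. If every control window lies before the programme, no control shares a calendar period with any participant. Period then determines group exactly, and no set of personal characteristics, however large, can separate the two. Any change in admission practice, bed use or demand between the control period and 2019 onwards would enter the primary comparison as programme effect.

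A background fall would be reported as benefit, and a background rise would conceal one. The cost comparisons are exposed in the same way. This is bias, so a larger sample does not reduce it. It is also distinct from the selection bias that the Discussion admits: two people with identical characteristics still differ if one is observed in an earlier year.

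**Working it through.** **Inputs.** From Sample Size Calculation: 32% of controls and 23% of the intervention group with a hospital visit in 180 days, two-group alpha 0.05, 80% power, 386 per group. From Data Analysis: 500 per group. From Study Design and Overview: 8 months, taken as 243 days. The drift sizes and winter uplifts below are assumptions; the article gives none.

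**The plan's own figure.** Two-sided test of two proportions, pooled variance, no continuity correction: n = [1.96·√(2·0.275·0.725) + 0.8416·√(0.32·0.68 + 0.23·0.77)]² / 0.09² = 385.2, rounded up to 386. This reproduces the stated figure.

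**False benefit under drift, event counts.** Treat 32% in 180 days as Poisson. Mean per person over 8 months: μ = −ln(0.68) × 243/180 = 0.5206, so 500μ = 260.3 events. With no programme effect and a relative background fall d, SE = √(1/260.3 + 1/(260.3(1−d))), and the probability of a significant benefit is Φ(−1.96 − ln(1−d)/SE). For d = 10%, SE = 0.0901, −ln(0.9)/SE = 1.170, and Φ(−0.790) = 0.215.

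**Same question with two proportions**, 32% against 32%(1−d), n = 500 per group:

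| Assumed background fall | False benefit, counts | False benefit, proportions |
|---|---|---|
| 0% | 2.5% | 2.5% |
| 5% | 8.3% | 7.9% |
| 10% | 21.5% | 19.5% |
| 15% | 42.8% | 38.3% |
| 20% | 67.0% | 60.8% |

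The two models agree closely. A 10% fall is 0.10 × 32 = 3.2 points, or 3.2/9 = 36% of the planned 9-point difference.

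**Opposite direction.** With the planned effect and a 10% background rise, the intervention rate becomes 0.23 × 1.10 = 25.3%. Power at 500 per group falls from 89.1% to 65.0%.

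**Season.** Count December to February months in an 8-month window. Starts from July to December contain 3 each; January 2, February 1, March 0, April 0, May 1, June 2. The average over a full year of starts is 24/12 = 2.0. Assume uniform enrolment over the 18 months from July 2019 to December 2020: (18 + 6 + 18)/18 = 42/18 = 2.33. With a winter uplift w, the ratio of arm means is (1 + 2.33w/8)/(1 + 2w/8), which is 1.004 for w = 10% and 1.012 for w = 30%. So against controls starting evenly through the year, the arms differ by 0.4% to 1.2%, with more winter in the intervention arm, hence against the programme. If all controls started in July to December (3 winter months), the intervention mean would be 0.8% to 2.2% lower. If all started in March or April (0 winter months), it would be about 3% to 9% higher.

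**Period to be matched.** Enrolment to the end of 2020 plus 8 months runs to about August 2021. If instead data collection ends in summer 2020 (taken as August), the last participant with full follow-up enrolled by about December 2019. The two statements differ by about a year.

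**The case against.** The strongest reply is that the control window is never dated. Drawing controls retrospectively is compatible with extracting records for the same months after the study, and historical records may describe the data source, not an era. The named matching variables are examples from more than 100, so an index date could be among the rest. The study-design figure is not available here, and a condensed article may leave index dates to the full protocol. This stands in part: a reader might infer that the controls are shown to precede the programme, and the article does not establish that. It does call the subscribers themselves historical, and what it states about design, tests and limitations contains no safeguard against the period effect that follows on that reading.

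Two further inferences go too far. One is that season alone could shift the comparison by 4% to 10%. That range contrasts the most extreme individual start months; across an arm enrolled over 18 months the shift is far smaller, as shown above. The other is that the absence of cost indexation is itself an error. The article states nothing wrong about prices, and a price year is a detail it may leave to the full plan.

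The Discussion does concede that the non-randomised retrospective control is a limitation that matching addresses only partially. That concession concerns which people are selected, not when they are observed.

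**Conclusion.** The concern holds conditionally. If control windows precede the programme, as the wording most plainly suggests, the planned comparison confounds calendar period with programme, and neither the matching described nor the unadjusted tests can undo it. The false-benefit rates of about 8% to 67% depend on assumed falls of 5% to 20% and on a Poisson reading of the 32% figure. They show sensitivity and are not a forecast; nothing in the article says whether drift is 1% or 20%, or in which direction. Season is a minor contributor unless control start months are concentrated. The conflict between the end of enrolment and the end of data collection does not change the conclusion, but it leaves the period to be matched undefined. This should be fixed before the control data are drawn; confidence is medium because the control window is undated.

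**What to change.** 1. In Study Design and Overview and in Data Analysis, state the calendar window of the controls. Draw them from TK-insured PERS subscribers outside the programme, and start each control's 8-month window in the same calendar month and year, plus or minus 1 month, as the matched participant's enrolment.
2. Where no same-year control can be found, use the same calendar month of the latest earlier year, adjust for the year-on-year change among non-participating subscribers, and express costs in one price year. That adjustment needs only group-level rates from concurrent non-participants, so it can be made even where a close individual match is lacking.
3. Keep the fully historical comparison as a sensitivity analysis.
4. Add calendar-time confounding to the limitations in the Discussion.
5. Reconcile the two end dates in the Results section.

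The cost is a changed query and matching rule on insurer reimbursement records; no new patients are needed. The candidate pool, now about 5000/500 = 10 per participant, would shrink. Some concurrent controls may have declined the programme, which could add to the selection bias already admitted, so known decliners should be flagged and examined in a sensitivity analysis.
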